### 3.4.3 Data Reporting

The means will be presented with their standard deviations. Relative risks and odds ratios will be presented with their 95% confidence Intervals. Two-tailed statistical analysis will be used and statistical significance will be defined at level of  $p < 0.05$ .

[figure not shown]

## A.8 QUALITY ASSURANCE

A.8.1 What procedures are in place to ensure the quality of the data?

*Guidance notes:*

*For qualitative data (for example) what procedures will be used to check translations or compare data obtained from different sources?*

*For quantitative data (for example) how will transcription errors be minimised?*

*Give some detail on how methods are going to be piloted, if appropriate*

- An instrument to collect the required data has been adapted from the tools used by other researchers in other sites.
- Computer-generated numbers will be used to randomize mothers into this study. These numbers will be in opaque envelopes to blind the observers on the group to which the next mother will be randomized and observed. The Investigator or researchers/ observers will not have prior knowledge of the treatment allocated to the next patient to avoid bias into the random allocation process.
- Details of the aim and procedures to be involved in the trial for the three groups, potential side effects and therapeutic benefits will be explained to the eligible patients on admission by the nurse research assistant before randomization occurs. Once the mothers consent to participate in the study, opaque envelopes containing computer-generated consecutive numbers from 001-320 will then be opened by the researcher and the random group allocation of the mothers will be communicated.
- Improved routines at the time of discharge will be observed for all mothers on the ward regardless of the study intervention. Family planning counseling and advice will be availed to all mothers at discharge.
- Routine reviews, counseling and support will be done to ensure adequate management of side effects and other family planning concerns that may arise during the course of the study.
- Internationally recognized brands of contraceptives or their equivalent from national Medical stores (NMS) will be used for this study
-

- Two Nurse research assistants will be **recruited** and **trained** as observers and data collectors to increase accuracy and consistency in documenting the needed data. They will be assisted by the post natal clinic staff and these research assistants will be blinded to the hypotheses of this study. To minimize observer bias and facilitate participant randomization, one nurse research assistant will deal with enrollment, family planning counseling and support while another will entirely follow up participants and collect the required data at different time points. Senior Obstetricians will supervise the trial and administration of contraceptives on post natal clinic.
- Mothers will be free to withdraw from one family planning method to another following their doctors advice.

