#### **I. Randomization:**

Consecutive numbers ranging from 001 to 320 will be computer generated to indicate the 2 main groups into which mothers can be randomly assigned and enrolled. These consecutive numbers will be labeled on top of the opaque envelopes. To be eligible, mothers must be HIV positive, have had a delivery within the last 48 hours, above 18 years of age, anticipating to begin family planning post partum, have a spouse/sexual partner whom we may contact or invite to participate in the study, must be mentally stable and qualify for any family planning method available. Once eligibility of a mother is confirmed, they will be invited to participate in the study.

The aim of the study and details of the procedures to be involved in the trial, potential side effects and therapeutic benefits will be explained before randomization occurs. Once the mothers consent to participate in the study, a study number will be allocated by the nurse research assistant (**who will be recruited to work on the ward/post natal clinic for this study**) by taking the next in a series of similar opaque envelopes provided to conceal allocation of groups. These opaque envelopes will be labeled with computer-generated list of numbers with group allocation (either Intervention group or Control Group) of the mothers randomized in blocks of 20. Nurse research assistants will be blinded to the group allocation until eligibility and study participation is confirmed. They will also be blinded to hypothesis of the study.

A blood sample will be drawn at baseline to confirm the HIV status and or do a CD4 cell count in case it is unknown at the time of enrollment. This will be done to support women enroll for the recommended Option B+ incase the women are not yet lifelong ART].

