A different study nurse will be enrolled and trained to specifically collect data from participants. The socio-demographic data and obstetric characteristics will be documented. Other documented potential covariates of contraceptive use like participant age, primary partner's age, primary partner's HIV status, personal and partner fertility desires, number of children, most recent CD4 cell count, Efavirenz-containing ART Regimen (due to its association in decreasing levels of hormonal contraception thus recommending dual methods and its teratogenicity concerns-although these concerns have been found to be exaggerated), socio-economic status, body mass index, education level, time on ART . Prior contraceptive use experiences, fertility desire/ pregnancy intentions or aspiration will be measured using the CDC pregnancy Risk Assessment Monitoring System Instrument (Ahluwalia et al., 1999)

Effective contraception use will be defined as consistent use [both self report and observational chart review from study nurse at the family planning clinic] of a family planning method (including consistent condom use) , including dual contraception (use of condoms and another contraceptive method-hormonal or permanent) for HIV-sero discordant couples/partners (for participants who know partner's status). A primary partner will be defined either as a regular spouse, who is also a regular sexual partner or the most recent sexual partner if no main partner is named. These sexual partners will also be enrolled and interviewed at baseline and at 1 year. In case a consented mother ends up with a serious adverse event, the time and indication will be documented and reported. In case a woman changes the contraceptive method, the reasons for the change will also be documented.

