5.2 Outline who will deliver the above information and how?

The information will be delivered by nurse Research Assistants of the study.

- They will share information about the study with the participants, i.e, introduce themselves, explain the purpose and type of the research to be carried out, and invite the participants to join the study, on a voluntary basis. This will be done at the post natal ward and before discharge. This will give the participants ample time to think through the consent process and make an informed decision without coercion.
- The RAs will also explain the procedures, risks and benefits, ensure confidentiality, dissemination of results, and whom to contact later, for further questions.
- They will provide a certificate of Consent to the participants for their signatures

B.5.3 Please indicate how consent will be obtained, given local circumstances.

*Guidance notes:*

*In some societies, the concept of giving consent on an individual basis is unfamiliar. It may be necessary to obtain consent both at community and individual level.*

*Obtaining consent from minors requires both consent from the guardian and, where possible, the minor.*

Consent will be sought on an individual basis and only adult mothers will be approached for possible participation in the study.

B.5.4 Are any inducements to be offered to either participants or the individuals who will be recruiting them? (e.g. improved patient care / cash) (please tick appropriate box)

|                          |                                     |
|--------------------------|-------------------------------------|
| Yes                      | No                                  |
|  |  |

B.5.5 If yes, please give details:

N/A

B.5.6 Outline any hidden constraints to consent.

*Guidance notes:*

*Examples where hidden constraints may be important include:*

- situations where participants are employees of the investigator
- patients who may feel their care could be compromised if they do not consent to research initiated by their carers.

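### After allocation the protocol relies on blinding nurses to the hypothesis, which is not credible for the nurse who takes consent, and states no masking to arm for the nurse who collects the outcomes.

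*Protocol*

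**What the plan says.** Three sets of statements in the protocol bear on who is blinded to what.

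- **Hypothesis.** The Randomization part of A.4 says of the nurse research assistants: "They will also be blinded to hypothesis of the study". A.8 repeats this for the two nurses to be recruited: "these research assistants will be blinded to the hypotheses of this study".
- **Allocation.** The Randomization part sets a time limit: "Nurse research assistants will be blinded to the group allocation until eligibility and study participation is confirmed". The envelope provisions in A.8 concern concealment of the next assignment, not masking afterwards.
- **Roles.** A.8 gives enrolment, counselling and support to one nurse, while "another will entirely follow up participants and collect the required data at different time points". The stated purpose of this split is to limit observer bias. A.4 agrees: "A different study nurse will be enrolled and trained to specifically collect data from participants".

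On consent, the Randomization part says that "The aim of the study and details of the procedures to be involved in the trial" are explained before randomization, along with side effects and benefits. A.8 says that these matters "will be explained to the eligible patients on admission by the nurse research assistant before randomization occurs". Under B.5, item 5.2, the nurse research assistants, in the plural, are to "introduce themselves, explain the purpose and type of the research to be carried out".

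A.5.4 names two primary outcomes: confirmed consistent use of an effective method at 12 months, and pregnancy desire. A.4 bases the first on self-report plus chart review by a study nurse at the family planning clinic, and measures the second with a named questionnaire instrument.

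**The concern.** The trial cannot blind the women, so what protection it has against biased measurement must come from those who record the outcomes. The protocol addresses this, but chooses the weaker safeguard. Keeping staff unaware of the hypothesis is hard to sustain when the aim, as A.3 gives it, is to test whether family planning support changes pregnancy intentions and contraceptive use. Anyone able to explain that to a patient can guess which result is hoped for.

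The stronger safeguard, keeping the outcome collector unaware of arm, is never stated, although the two-nurse structure it needs is already planned. A collector who knows the arm may probe differently, apply a different threshold for consistent use, or read a chart differently. Such differences enter the treatment comparison directly, and analysis by intention to treat does not remove them.

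**Working it through.** **1. Who can be blinded to the hypothesis.** The enrolling nurse explains aim, procedures and benefits (A.8) and gives the counselling and support (A.8). Hypothesis blinding is not credible for her. For the data nurse the evidence is weaker: only the plural in item 5.2 could bring her into consent, and the division of labour in A.8 points the other way.

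**2. Who is masked to arm after allocation.** The only statement on allocation ends when participation is confirmed. The passages that introduce the data nurse separate her from enrolment and support but do not say that she is unaware of arm.

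**3. How she could learn the arm.**
- A.4 has intervention women contacted at 6 months by a study research assistant to start family planning. An interview falls at the same time, and the protocol does not say which assistant makes the contact.
- A.5.4 ties up to 160 partners to the intervention group. Whoever interviews a partner could infer the arm, but the interviewer is not named.
- A.6.3 lists administering methods and collecting data as tasks of the same category of staff.

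**4. Which outcome parts are exposed.** Pregnancy desire is an interview answer. Contraceptive use has an interview part and a chart part; deciding whether use was consistent needs judgement, and the chart reviewer is not stated to be masked either.

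**5. The plan's own figure.** A.5.4 gives 156 per group for 45% against 63%, 90% power, 5% level. With unpooled variance and a two-sided test:

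n = [0.45×0.55 + 0.63×0.37] × (1.960 + 1.282)² / 0.18² = 0.4806 × 10.51 / 0.0324 ≈ 156.

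It reproduces, and nothing here changes it.

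**6. Illustration of size.** Inputs: 45% use (A.5.4), 160 women per arm (A.4, 320 randomized equally), two-sided 5% test (A.7). The recording shift d is an assumption with no source in the documents. With no true effect, set p1 = 0.45, p2 = 0.45 + d, p̄ = (p1 + p2)/2, and

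SE0 = √[2p̄(1−p̄)/160], SE1 = √{[p1(1−p1) + p2(1−p2)]/160},

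P(reject) = Φ[(d − 1.96·SE0)/SE1] + Φ[(−d − 1.96·SE0)/SE1].

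For d = 0.05: SE0 = 0.0558, SE1 = 0.0558, giving Φ(−1.07) + Φ(−2.86) ≈ 0.145. For d = 0.10: SE0 = 0.0559, SE1 = 0.0556, giving Φ(−0.17) + Φ(−3.77) ≈ 0.432.

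| Assumed shift | Contraceptive use, base 45%, shifted up | Pregnancy desire, base 33%, shifted down |
|---|---|---|
| 0 points | 5.0% | 5.0% |
| 2 points | 6.5% | 6.7% |
| 5 points | 14.5% | 16.3% |
| 8 points | 29.8% | 35.1% |
| 10 points | 43.2% | 51.3% |

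The 33% is the desire rate quoted in A.5.4. To judge plausibility for contraceptive use: a shift of 5 or 10 points means misrecording 5/55 = 9% or 10/55 = 18% of non-users, in one arm only.

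**The case against.** The best defence is that the protocol already splits the roles in order to limit observer bias, confirms contraceptive use from charts, and measures pregnancy desire with a named instrument. All three help. None is masking: a separate nurse may still know the arm, and the chart reviewer is also a study nurse with no stated masking.

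Several stronger readings are tempting, and the documents do not support them.

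- *The data nurse is unmasked.* No text says so. It would be an inference from silence and from a time limit that sits beside the description of the nurse handling the envelopes. What can be said is that masking is not stated.
- *Consent makes hypothesis blinding impossible for all nurses.* The conflict is clear only for the enrolling nurse. Explaining an aim is also not literally disclosing a directional hypothesis.
- *Both primary outcomes are purely self-reported.* Contraceptive use also requires chart review.
- *Any bias must favour the voucher arm.* That is the most plausible direction, but nothing in the protocol fixes it.
- *Partner interviews will reveal the arm to the data nurse.* That holds only if she conducts them, which is not stated.

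It is also fair to object that the rejection rates attribute the whole shift to the assessor. Women know their arm, and their own reporting bias would survive masking. The table therefore does not measure what masking would gain.

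**Conclusion.** The point holds in a limited form. The only blinding planned after allocation is to the hypothesis; it is not credible for the nurse who informs women and delivers the support, and it may or may not hold for the nurse who collects the data. Masking of that second nurse to arm is unspecified. Pregnancy desire and the self-report and judgement parts of contraceptive use are the exposed components.

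The size is unknown. The rates of about 15% and 43% show how sensitive the test is to shifts of 5 and 10 points, under the stated assumptions of no true effect, 45% use and 160 per arm. They do not estimate the bias to be expected. Who is masked is a matter of conduct and has to be settled before the first follow-up interview, so the protocol should be changed.

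**What to change.** In the Randomization part of A.4 and in A.8:

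- Stop relying on hypothesis blinding for the enrolling and support nurse.
- State that the follow-up nurse is masked to allocation, takes no part in consent or support, and has no access to the envelopes, allocation log, voucher records or SMS list.
- Have her ask the primary outcome questions before any question on vouchers, reminders or partner participation, and before she has any contact with partners. Handing partner interviews to the support nurse is not recommended, since it would undo the separation of support from data collection that A.8 sets up.
- Apply a fixed definition of consistent use to the chart data, without arm information where feasible.
- Record each instance of unmasking.

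The cost is protocol wording, interview order and control of the allocation records. The two nurses are already planned, so no staff are added. Chart review without arm information may need some rearrangement at the family planning clinic, which is why it is asked for only where feasible. The downside is that masking will be partial, because women know their arm and may reveal it. The sample size is unaffected.

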#### A.9 DISSEMINATION OF RESULTS

Please outline what plans you have for dissemination of results.

*Guidance notes:*

*Where possible a mechanism should be in place to inform study participants of the outcomes of the study.*

*It is important that study findings are made known to local services / policy makers before they are discussed (e.g.) at international scientific meetings*

Particularly, the dissemination of results for this study is motivated by both the academic and social impact, with a focus on the practical benefits for the key stakeholders. The following points are highlights of the approach:

- Presentation of the project on the MUST website [if possible]  
[www.must.ac.ug/research](http://www.must.ac.ug/research)
- Local meetings with key stakeholders in health policy, pharmaceutical sector, and other sectors of civil society and government
- Presentations at institutional, national and international conferences
- Specially tailored open-source materials (such as policy briefs, articles for magazines that reach policymakers or presentations to policymakers)
- Dissemination of research findings through information networks operating at various levels
- Submission and publication of research findings to international peer-reviewed journals
- Dissemination of research reports and other project outputs on an open section of the website.

[figure not shown]

## SECTION B

### CONSEQUENCES FOR THE LOCAL COMMUNITY / ENVIRONMENT AND PARTICIPANTS

B.1 Outline the potential adverse effects, discomfort or risks that may result from the study in the following areas:

#### B.1.1 Participants

*Guidance note:*

*In addition to the physical effects of tissue sampling (for example blood sampling) it should be borne in mind that interviews and focus group discussions may sometimes trigger painful or distressing memories (e.g. questions about sexual practice or the death of a child)*

1. There are some questions that will be asked and have been classified 'sensitive or personal'. In case the participants feel some anxiety answering some of them, they may choose not to answer some questions they feel uncomfortable
2. There is the risk of discomfort and or pain when a contraceptive method is being administered or a blood sample for HIV testing and CD4 cell count is being drawn. There is also a small risk of bruising, scarring or infection. However, care will be taken to professionally administer these routinely used methods with good infection prevention techniques. A participant may also refuse a particular contraceptive method and chose another that makes her comfortable at any time.
3. There is a risk of side effects following administration of these contraceptive methods, like longer periods, dysmenorrheal, acne, weight gain, etc. In case this happens, routine procedures will be followed to give the participant additional family planning support, counseling and advice, therapeutic medications or procedures to change, treat or prevent further occurrences. Trained health professionals will also be available during the study to provide professional advice and answer any further questions

### B.1.2 Investigators

Guidance notes:

Include here (for example)

- the biomedical risks to investigators (including local staff) involved in tissue sampling (e.g. Hepatitis B, HIV)
- the psychological consequences for social science investigators exposed to narratives of violence or severe grief
- the risks from the environment (e.g. in a war zone)

There are anticipated risks to Hepatitis B or HIV especially since the study is targeting administration of the family planning method among HIV positive women.

### B.1.3 Members of the public

We do not expect any adverse effects, discomfort or risks to members of the public.

## B.2 Outline what steps will be taken to minimise the adverse effects, discomfort or risks described above.

### B.2.1 For participants

Guidance notes:

*In biomedical research, appropriate use of anaesthesia prior to procedures (for example) is important.*

*For social science research it may be necessary to ensure that counselling services are available for those who re-live traumatic experiences through (for example) an in depth interview.*

- There are some questions that have been classified 'sensitive or personal', that may cause the participants to feel some anxiety answering some of them. In this case, they may choose not to answer questions they feel uncomfortable
- The risk of discomfort, bruising, scarring or infection when contraception is administered or a blood sample is being drawn will be minimized by engaging highly trained personnel in offering family planning services.
- The risk of side effects following contraceptive administration for the intervention groups will be managed by following routine procedures to give the participant support, counseling, advice or additional therapeutic medications or procedures to treat or prevent effects. Trained health professionals will also be available during all post natal visits to answer any further questions
- The nurse research assistants will not discuss any information obtained from the participant with anyone other than the research and health care team
- Refusing to participate in this study at any time will not affect healthcare services that a participant would ideally obtain from the hospital.

[figure not shown]

B.2.2 For investigators

*Guidance notes:*

*Where the research may involve adverse experiences for investigators (see B.3.2), de-briefing / support meetings may be important.*

Protective gear like aprons and gloves will be readily provided and availed for clinic staff at all times to prevent any risk of HIV transmission during administration of contraceptives and drawing a blood sample

Procedures to obtain post exposure prophylaxis will also be streamlined and services availed to all staff at all time through the routine hospital policy.

Training on infection control will be done and emphasized for all the staff involved in this study.

B.2.3 For members of the public

**ADVERSE EXPERIENCES ARE NOT EXPECTED**

**B.3 CONSEQUENCES FOR LOCAL HEALTH SERVICES**

B.3.1 What demands will this research place on local health services?

*Guidance notes:*

*For example, how much of a nurse's usual work time will be taken up in acting as an interpreter for an outside investigator?*

During the study, which is expected to last a period of about 2 years, the nurse RAs may require to use the routine office space at the maternity ward, post-natal ward and post-natal clinic to contact, randomize, enroll and or document observations. They may also take up some available working space and use the available shelves to keep contraceptives. The nurse RAs may also require assistance from fellow nurses/midwives in administering contraceptive methods or taking required observations. Nurse research assistants speaking the local language will however be recruited for this study

B.3.2 Detail how the design of the research project takes into account the demands described in 3.1.

*Guidance notes:*

*Disruption to routine services should be kept to a minimum.*

The study will not disrupt the routine services. All contraceptive methods to be used in this study are routinely used and recommended by the MoH. NMS also routinely supplies them to health centers. These include; condoms, injectables, contraceptive pills, IUDs and hormonal implants.

